### Outcome measures

#### Primary outcome

The number of days alive without unplanned hospitalisation within 1 year of follow-up is derived from the number of unplanned hospital days as collected in the HF registry (table 1).

**Table 1 T1:** Operationalisation of exposure variable and study outcomes

Variable	Source	Time of collection	Operationalisation
Exposure			
Telemedicine	HF registry, telemedicine-generated data	T0, T1*, T2	Whether a patient receives telemedicine. Five categories: (1) no telemonitoring†; (2) telemonitoring by telephone; (3) telemonitoring, non-invasive based on traditional parameters (eg, blood pressure, ECG); (4) telemonitoring using ICD based on HF parameters; and (5) telemonitoring, invasive using sensors in the bloodstream or heart.
Primary outcome			
Number of days spent alive without unplanned hospitalisations within 1 year of follow-up	HF registry	T1*, T2	Number of days directly related to unplanned cardiac hospital admission due to HF. Number of admission days will be summed up over a period between follow-up moments and subtracted from 365 days.
Secondary outcomes			
Costs	Derived from HF registry, external data source, EHR, interviews	T0, T1*, T2	Costs estimated from patient, disease and treatment characteristics. Information taken into account includes medication use, whether the patient underwent cardiac interventions (eg, pacemaker implantation, percutaneous coronary intervention), use of telemedicine, hospital admission days, visits to the outpatient clinic, visits to the emergency room, admission days at an intensive care unit and visits to the GP related to HF.
All-cause mortality	HF registry, external data source	T1*, T2	Mortality status, determined after verification at the Personal Records Database (in Dutch: Basisregistratie Personen). Mortality is independent of HF (all-cause).
Functional status	HF registry	T0, T1*, T2	NYHA classification: a functional classification of patients based on severity of symptoms and physical activity, with specific attention to fatigue, palpitation and dyspnoea. Scores are linked to one of four NYHA classes: class I: no limitation; class II: slight limitation; class III: marked limitation; and class IV: unable to carry on any physical activity without discomfort.^1^

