### Exposure measurement

Exposure to telemedicine is measured in the HF registry at 6 months and 12 months of follow-up as non-use of telemedicine, telephone only, non-invasive telemedicine, implantable cardioverter defibrillator-based telemedicine or invasive telemedicine (table 1). Telemedicine output can be different from the closed-ended interviews that correspond to all outpatient clinic contacts in general. The components of the telemedicine intervention will be assessed at the hospital level at one time during the follow-up period. Table 2 provides an overview and operationalisation of the main components of the telemedicine intervention that have been described in existing literature or at the local (eg, hospital) level.^7 32–34^ The components will be validated and possibly further refined based on the interviews. Figure 3 illustrates the flow of data collected at the hospital level and at the patient level.

**Table 2 T2:** Overview and operationalisation of telemedicine variables collected in the qualitative study

Component	Definition	Operationalisation (examples)
Supplier	(External) supplier of telemedicine for patients with HF.	Sanacoach, Luscii, Motiva/Philips, linked in personal environment in EHR.
Purpose of telemedicine	The intention/motives for which the telemedicine intervention is administered: patient level and/or hospital level.	Monitoring, prevent exacerbation, reduce workload, reduce costs, patient-centred care.
Considering telemedicine	First time a clinician considered telemedicine in HF management.	After diagnosis, (re)hospitalisation, titration phase.
Structured telephone support	Structured monitoring by telephone without using applications or devices specific to telemedicine and monitoring HF.	Present or not present.
Applications	Technologies or platforms on which the patient could receive telemedicine.	Smartphone, tablet, laptop, television, smartwatch.
Devices	Accessory a patient could use to perform telemedicine.	Blood pressure device (with or without Bluetooth), weight scale (with or without Bluetooth), smartwatch.
Involved healthcare workers	Involved healthcare workers and their role in considering and executing telemedicine.	HF nurse, nurse specialist, cardiologist.
Control centrum	The presence or absence of a control centrum to check the submitted measurements and questions.	Present or not present.

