##### Preparation of the statistical model

As a first step, we describe how the overall effect of offering any type of telemedicine versus not offering telemedicine will be estimated. This analysis will subsequently be used for a comparison of telemedicine effects on days alive without unplanned HF-related hospitalisation during 1 year across subgroups.

The cohort is restricted to individuals with newly diagnosed HF, that is, at most 3 months prior to baseline. The exposure contrast is defined as offering any type of telemedicine after first presentation with HF at the hospital outpatient clinic versus patients not offered telemedicine. The telemedicine status for the entire follow-up is defined by 6 months after baseline measurement of telemedicine, used as an observational analogue of an ‘intention to treat’ analysis in which the stopping of telemedicine is disregarded.

Because telemedicine administration is dependent on patient characteristics, confounding by indication will be accounted for. Based on clinical consensus, the following patient-level confounding variables measured at baseline will be adjusted for: age, sex, SES, BMI, NYHA, LVEF, aetiology of HF, systolic blood pressure, diastolic blood pressure, heart rhythm, heart rate, chronic respiratory disorders, OSAS, stroke, extra cardiac arterial vascular pathology, DM, hypertension, anaemia, CKD, malignancy, heart rhythm disorders, depression and thyroid disease (see table 3 and online supplemental material 1).

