The primary outcome model is a linear mixed model with a random intercept for the participating centre and is specified as follows. The outcome is measured in days, and because the final measurement may be less or more than 365 days after baseline, we rescale the number of days of unplanned hospitalisation to the number of days under follow-up to 365 days. The outcome is computed by subtracting the days of unplanned hospitalisation or death from 365. The earlier described confounding variables are added to the primary outcome model to adjust for confounding. Continuous covariates are modelled using splines. Multicollinearity between confounding variables and the telemedicine status is evaluated. The coefficient for telemedicine in the primary outcome model represents the average treatment effect of offering any telemedicine within 3 months after HF diagnosis compared with not offering telemedicine on days with unplanned HF-related hospitalisation during a year in the population of patients with newly diagnosed HF. Robust SEs are estimated to compute CIs.

For the secondary outcome functional status, a similar approach is taken to estimate the average treatment effect of offering any telemedicine within 3 months after HF diagnosis compared with not offering telemedicine on functional status after 1 year in the population of patients with newly diagnosed HF. For this analysis, the outcome model is a multinomial regression model, and baseline functional status is added as a covariate. The risk difference relative to the reference outcome category is assessed using the predicted outcomes of the primary outcome model offering of telemedicine versus not offering, to obtain the marginal risk difference.^38–40^ Similarly, for the secondary outcomes health status and hrQoL, the outcome model is a probit regression model, with baseline measurements added as a covariate. Healthcare utilisation will be assessed using a Poisson regression model, and all-cause mortality will be assessed using binary logistic regression.

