We plan to perform the following additional analyses. First, we plan to perform the analysis with the start of follow-up defined at the T1 (after 6 months) measurement and the outcome of unplanned hospitalisation days during 6 months. This is because telemedicine status can be misclassified when it is started shortly after baseline but is not registered in the data. Second, we plan to perform a per-protocol analysis of telemedicine use if detailed information on starting and stopping of telemedicine is available through linkage. Finally, we plan to perform all analyses in the entire cohort, rather than the cohort restricted on HF diagnosis, to a maximum of 3 months prior to T0 (baseline).

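### The additional analysis starting at T1 has no covariate for hospital days in months 0-6, so admissions that prompted telemedicine can confound it; report it with and without them

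*Protocol article*

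**What the plan says.** The additional analyses, at the end of the section on preparing the statistical model, include one with "start of follow-up defined at the T1 (after 6 months) measurement and the outcome of unplanned hospitalisation days during 6 months". The reason given is that "telemedicine status can be misclassified when it is started shortly after baseline but is not registered in the data".

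The covariates come from earlier in the same section: "the following patient-level confounding variables measured at baseline will be adjusted for: age, sex, SES, BMI, NYHA, LVEF", and so on through 23 items. None is a prior admission or a count of hospital days. For the outcome model the article says "The earlier described confounding variables are added to the primary outcome model to adjust for confounding". Nothing is added for the T1 analysis.

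Three other places bear on this:

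- The same section takes telemedicine status from the 6-month measurement.
- Table 1 collects hospital days at T1 and T2: "Number of admission days will be summed up over a period between follow-up moments and subtracted from 365 days". The months 0-6 days are therefore known at T1.
- Table 2, in the row on when telemedicine is first considered, gives as examples "After diagnosis, (re)hospitalisation, titration phase".

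**The concern.** Moving the start of follow-up to T1 puts the admissions of months 0-6 before time zero. They become part of the patient's history, like any other baseline characteristic. If an admission in that period led a clinician to offer telemedicine, the patient is classed as a user at T1 and, having been admitted recently, is plausibly at higher risk of another admission in months 6-12. Users would then look worse for a reason unrelated to telemedicine.

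Reading the confounder list at T1 instead of T0 does not close the gap, because the list has no hospitalisation item at either time.

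What is at stake is how the check is interpreted. It exists to show whether misclassified telemedicine status affects the main result. If the two analyses disagree, readers will tend to blame misclassification, although uptake after an admission could explain the difference. With a single version of the T1 analysis the two explanations cannot be told apart.

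**Working it through.** **The plan's own figures.** No sample size, power or effect is stated for the T1 analysis. The only scale available is the sample size section: 6.4 days (SD 21.1), 5% type I error, 80% power, 20% dropout. Assuming a two-sided test and equal groups, this gives 171 per group, 342 in total, and 342/0.80 = 428 (430 with the t-test version), close to the stated 432. Then 432 x 12 = 5184 and 5184/0.80 = 6480, as stated. Half of 6.4, or 3.2 days, serves below as an assumed 6-month effect.

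**Size of the confounding.** The article gives none of these inputs, so all are assumptions. Let p be the share admitted in months 0-6, u1 and u0 the uptake of telemedicine with and without such an admission, and g the extra hospital days in months 6-12 among those previously admitted.

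- Share admitted among users: s1 = p·u1 / [p·u1 + (1-p)·u0]
- Share admitted among non-users: s0 = p(1-u1) / [p(1-u1) + (1-p)(1-u0)]
- Bias = (s1 - s0) × g

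| p | u1 | u0 | g | s1 | s0 | Bias (days) | Share of 3.2 |
|---|---|---|---|---|---|---|---|
| 15% | 45% | 25% | 5 | 0.241 | 0.115 | 0.63 | 20% |
| 10% | 35% | 25% | 3 | 0.135 | 0.088 | 0.14 | 4% |
| 20% | 40% | 20% | 8 | 0.333 | 0.158 | 1.40 | 44% |

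With p of 10-20%, u0 of 20-25%, an uptake excess of 10-20 percentage points and g of 3-8 days, the bias runs from 0.14 to 1.40 days against telemedicine. A wider excess gives more: 45% versus 20%, with p = 20% and g = 8, gives (0.360 - 0.147) × 8 = 1.71 days. With no excess uptake after admission, the bias is zero.

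**Does adjustment repair it?** This was simulated with 400,000 patients per scenario. The assumptions were 0.25 admissions per patient per half-year, a mean stay of 9 days, unmeasured severity varying between patients, and a 25% reduction in admissions on telemedicine. The true effect is about 0.25 × 9 × 0.25 = 0.56 fewer days.

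| Setting | Unadjusted | Adjusted for months 0-6 days |
|---|---|---|
| Admissions prompt telemedicine (40-50% uptake after admission versus 10-20% without, among those not already started) | -0.23 to +0.70 | -0.32 to -0.47 |
| Mostly or all started at baseline, no prompting by admission | -0.54 to -0.58 | -0.50 to -0.11 |

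In the first setting the unadjusted estimate is biased and can change sign; adjustment removes most of the bias but not all. In the second the unadjusted estimate is close to the truth, and adjustment pulls it towards zero because the months 0-6 days already carry part of the effect.

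**Precision.** If exposure is unrelated to months 0-6 days, the standard error shrinks by the factor √(1 - ρ²): 0.995, 0.954 and 0.866 at ρ = 0.1, 0.3 and 0.5. In the simulation, with correlations of 0.12 to 0.38, the ratio of adjusted to unadjusted standard error was 0.93 to 1.01. The gain is therefore at most about 7% there and can vanish.

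**The case against.** **The post-exposure argument is the strongest, and it stands.** The article describes the effect as that of telemedicine offered within 3 months of diagnosis, and the check is aimed at telemedicine begun shortly after baseline. For those patients most of months 0-6 follows the start, so the hospital days are an early outcome and adjusting for them can do harm. This rules out replacing the planned model with the adjusted one. It does not rule out showing both.

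**The article may simply be silent.** It gives the additional analysis one sentence and a reason, and a fuller plan may say more. But it sets out its confounders item by item and says that the analysis is rerun from T1. Followed as written, the T1 model contains no admission history.

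**The evidence for admission as a trigger is thin.** (Re)hospitalisation is one of three examples for a hospital-level interview item, and it may include admissions at or before T0. That limits the claim to possible confounding of unknown size.

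Some stronger readings are tempting, but the document does not support them:

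- *The T1 result is certainly confounded.* This depends on the share of users who started after an admission, which is not given.
- *The check exchanges misclassification for a new problem.* The main analysis also reads telemedicine status at T1, and its 12-month outcome includes the months 0-6 admissions themselves. The difficulty is already there.
- *Precision is being lost.* No within-patient correlation is given, and the gain can be nil.
- *The plan contradicts itself by adjusting other outcomes for their baseline value.* For health status and quality of life it does so ("with baseline measurements added as a covariate"), and for functional status likewise, but those are T0 values. Table 1 has no T0 value for hospital days, and days accrued between T0 and T1 are a different kind of covariate.

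The planned per-protocol analysis would use start and stop dates, but only if linkage supplies them, and it answers a different question.

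**Conclusion.** The concern holds in a conditional form. The T1 analysis, as written, leaves out months 0-6 hospital days that the registry will already hold, while the article names (re)hospitalisation as an occasion for considering telemedicine. For patients who started after an admission this can bias the result against telemedicine, by about 0.1 to 1.4 days under the assumed inputs (4% to 44% of an assumed 3.2-day effect). For patients who started early, adjustment can bias it towards no effect. The mix of the two groups is unknown, so neither version alone can be trusted. This affects an additional analysis, not the primary one, but one on which the plan relies to judge misclassification. The benefit of the change is interpretability; no gain in precision should be claimed.

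**What to change.** In the paragraph on additional analyses, state that the T1-start analysis is reported in two versions: with the T0 covariates only, and with unplanned hospital days in months 0-6 added.

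The data collection section plans to record the telemedicine start date at patient level. Where it is available, either count only the days before the start for users, or compare patients who started after an admission with early starters as a check. Days before the start cover a shorter window for users than for non-users, so this is a supporting analysis and not a replacement.

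Add that neither version is presented as the unbiased one, and that a difference between them is not to be read as evidence of misclassification.

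The cost is a few sentences and one extra model. The hospital days need no new data collection, and the start dates are already planned. The downside is that the adjusted version may remove part of an early telemedicine effect, which is why both are shown.

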##### Research question 1: effectiveness of telemedicine in patient subgroups

Research question 1 investigates the effectiveness of telemedicine across subgroups of patients with HF. Patient-related subgroups were identified by a systematic literature review of randomised controlled trials (RCTs) of telemedicine: age, severity of HF (NYHA class at baseline), sex, SES, presence of depression, atrial fibrillation and type of HF (HF with preserved ejection fraction (HFpEF), HF with midrange ejection fraction (HFmrEF), HF with reduced ejection fraction (HFrEF)) (table 3).^20–24 41–49^ Stratified analyses of the primary outcome model are performed to estimate the above-defined average treatment effect in each of the subgroups. Heterogeneity in telemedicine effect across age is assessed on a continuous scale, where an interaction between age and telemedicine status is added to the primary outcome model, and the expected number of days out of hospital across age ranges from 50 to 90 years is predicted from this model under telemedicine offered versus not offered.

In an additional analysis, heterogeneity across time since diagnosis is explored for the entire cohort, without restricting to patients with a maximum of 3 months since HF diagnosis at baseline (diagnosed ≤3 months before baseline compared with >3 months before baseline).

The secondary outcomes functional status, health status and hrQoL are assessed using similar approaches but using multinomial, probit and probit regression model, respectively. Healthcare utilisation will be assessed using a Poisson regression model, and all-cause mortality will be assessed using binary logistic regression.

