### Study population

The HF registry comprises patients admitted to a Dutch hospital or to an outpatient clinic for HF irrespective of telemedicine use (figure 1). All patients who meet the diagnostic criteria for HF and its phenotype, according to the European Society of Cardiology (ESC) 2021 guidelines on HF, are included.^1^ If a patient has been diagnosed with HF in a setting other than the one where the patient currently presents (primary, secondary or tertiary care), the patient will also be included.^31^ Current HF registry is not yet incorporated and implemented in care pathways in EHR systems; therefore, selected patients fulfilling the NHR criteria are included in the HF registry and not on a consecutive basis or full coverage of all patients at the outpatient HF clinic. This may lead to selection bias. To prevent this selection bias, a researcher of RELEASE-HF is alerting healthcare professionals regularly to include all patients with HF in the HF registry, regardless of their telemedicine use, treatment and disease severity. Additionally, national working groups are progressing to fully incorporate the HF registry into the EHR.

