### Data collection and quality control

Data of the HF registry will be remotely monitored for major outliers and missing variables using the NHR; these processes have been described elsewhere.^30 35^ The NHR uses a unique individual patient identifier (NHRpersonID) to deduplicate registrations of the same patient (at the same or different hospitals) in the HF registry.^36^ During the RELEASE-HF study, researchers will perform an additional check on completed data and provide assistance to hospitals to reduce missing values, as well as assistance to reduce registration burden.

Telemedicine interviews, using an interview guide with closed-ended questions, will be performed by a RELEASE-HF investigator and conducted with clinicians (eg, cardiologist, HF nurse, nurse specialist, physician assistant). Interviews will be held during the 36-month period of data collection. All hospitals with telemedicine in HF care will be interviewed once, and the data will be checked with the hospitals once during the data collection period to be aware of changes in the components and status of telemedicine. For each hospital, the 6-monthly costs of telemedicine are determined via interviews and registration data (if at hand). The units will be linked to the unit cost guideline provided by the Dutch National Health Care Institute (Dutch: Zorginstituut Nederland).^37^ These interviews will be performed by a health technology assessment (HTA) scientist and conducted with clinicians or finance department staff. All participants will provide informed consent.

Patient-level telemedicine data are collected by a clinician, data manager or researcher at the hospital where the patient is being treated because these individuals have access to the identification log of the HF registry. Collected data will include the start date of telemedicine use and the frequency at which measurements are sent to the treating hospital, with a high rate typically referred to as a high-intensity (or acute) protocol and a low rate as a low-intensity (or stable) protocol.

The Heart4Data consortium will establish opportunities for data linkage between the HF registry and other national registry databases, in collaboration with public partners (figure 2).^28^ At the time of writing, a collaboration between these databases and the HF registry is not yet established for all external national databases.

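### The entire-cohort and time-since-diagnosis analyses do not separate patients already on telemedicine before baseline, so the comparison of ≤3 with >3 months since diagnosis risks prevalent-user bias of unknown size and direction

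*Protocol article*

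**What the plan says.** The Protocol article, under Preparation of the statistical model, limits the main analysis: "The cohort is restricted to individuals with newly diagnosed HF, that is, at most 3 months prior to baseline". The contrast is "offering any type of telemedicine after first presentation with HF at the hospital outpatient clinic versus patients not offered telemedicine". On timing of exposure: "The telemedicine status for the entire follow-up is defined by 6 months after baseline measurement of telemedicine". Later stopping is disregarded, as an observational analogue of intention to treat. The same section states the target effect as that of an offer made within 3 months after diagnosis.

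Two additional analyses then drop the limit on time since diagnosis. The first is general: "Finally, we plan to perform all analyses in the entire cohort, rather than the cohort restricted on HF diagnosis". The second, under Research question 1, is specific: "heterogeneity across time since diagnosis is explored for the entire cohort, without restricting to patients with a maximum of 3 months since HF diagnosis". It compares patients diagnosed up to 3 months before baseline with those diagnosed earlier.

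The Study population section admits previously diagnosed patients ("If a patient has been diagnosed with HF in a setting other than the one where the patient currently presents") and says that the registry takes patients whether or not they use telemedicine.

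On the data available, Table 1 lists telemedicine status at T0, T1 and T2, while the Exposure measurement section names only 6 and 12 months. Data collection and quality control adds: "Collected data will include the start date of telemedicine use". Information on starting and stopping is given an analytic use only in a per-protocol analysis, which depends on linkage.

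**The concern.** With diagnosis at most 3 months before T0, any telemedicine use before baseline is short. Once the limit is lifted, prior use has no upper bound. A patient diagnosed years ago and on telemonitoring for much of that time counts as exposed if still on it at T1. A patient who tried it and gave it up before T0 counts as unexposed, unless it was restarted.

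This has three consequences:

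- The longer-diagnosed exposed group may be partly selected for having tolerated and kept telemedicine.
- Its baseline covariates (NYHA class, blood pressure, the SF-derived depression score) may already reflect the intervention. Adjusting for them can remove part of the effect, and it does not undo the selection.
- The two strata need not estimate the same quantity, so a difference between them cannot be read simply as a timing effect.

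The Introduction names how, when and in whom telemedicine should be given as the gap in knowledge. Among the planned patient-level analyses, this comparison is the one that bears on when in the disease course telemedicine helps.

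**Working it through.** **Step 1. Who can enter the longer-diagnosed stratum.** Eligibility requires a diagnosis more than 3 months before T0 and sets no condition on earlier telemedicine. Exposure depends only on T1 status. Four histories are therefore possible:

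| Telemedicine before T0 | Status at T1 | Classified as |
|---|---|---|
| None | On (started after T0) | Exposed |
| Started, continued | On | Exposed |
| None | Off | Comparator |
| Started, stopped before T0 | Off | Comparator |

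The second and fourth rows are the problem. The protocol's intention-to-treat analogue disregards stopping, but in the fourth row stopping decides the exposure group.

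**Step 2. Match with the stated effect.** The effect is that of an offer within 3 months after diagnosis. For a patient diagnosed more than 3 months before T0, such an offer must precede T0. Read literally, every exposed patient in this stratum would have been offered telemedicine before baseline. Read by T1 status, the group is a mixture. Neither reading gives the contrast estimated in the recently diagnosed stratum.

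**Step 3. The plan's own yardstick.** The sample size section plans on 6.4 days (SD 21.1) and interactions of 50% to 60% of that: 6.4 × 0.5 = 3.2 and 6.4 × 0.6 = 3.84 days. Its totals also hold together: 432 × 12 = 5184, and 5184 / 0.80 = 6480. No figure is given for the time-since-diagnosis comparison itself.

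**Step 4. Possible size, on assumed inputs.** Suppose the true effect is 6.4 days in both strata. Let s be the share of longer-diagnosed exposed patients who started before T0. Let b be their difference, in days, from new starters in prognosis left after adjustment. With no such users in the other stratum:

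spurious heterogeneity = (6.4 + s × b) − 6.4 = s × b

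| s | b = 0 | b = 2 | b = 5 | b = 10 |
|---|---|---|---|---|
| 0.25 | 0 | 0.5 | 1.25 | 2.5 |
| 0.50 | 0 | 1.0 | 2.5 | 5.0 |
| 0.75 | 0 | 1.5 | 3.75 | 7.5 |

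If 10% of the comparator are former users who do worse by b days, add 0.1 × b; for s = 0.5 and b = 5 this gives 2.5 + 0.5 = 3.0. If a share s0 of the exposed in the recently diagnosed stratum also started before T0, the expression becomes (s − s0) × b; with s = 0.5, s0 = 0.25 and b = 5 it is 1.25. The sign of b is not known. It would be negative if sicker patients were the ones kept on telemonitoring.

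**Step 5. Check by simulation.** The true effect was set to zero. Half of the patients had started before T0, and a fifth of those not on telemedicine at T0 started afterwards. About 75% of the exposed were then continuing users. The apparent benefit was 0.0 days when stopping was unrelated to frailty, and 1.6 or 2.8 days when frailer patients stopped more often (weaker and stronger dependence). New starters against non-users gave between −0.1 and 0.1 days in every setting, which supports a restriction to new users.

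**The case against.** The strongest objection is that bias is possible but not shown. The documents give no share of users who started before T0, no stopping rate and no prognostic difference. That stands. A reader might infer that the longer-diagnosed stratum simply compares persistent users with others and that its result is biased. The documents do not support this, because exposure is read at T1, so patients who started after T0 are in the exposed group too.

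A reader might also build a larger example. Suppose 30% ever used telemedicine and 20% are at high risk and lose 35 more days a year. Suppose half of the high-risk users and a fifth of the others stop before T0. The high-risk share is then 0.030 / 0.222 = 13.5% in users and 0.170 / 0.778 = 21.9% in non-users, a difference of 8.3 points before rounding, or 2.9 days. This should not be offered as the likely size. It ignores adjustment for more than 20 baseline variables. Its single risk factor has variance 0.2 × 0.8 × 35² = 196, which is 44% of the planning variance of 21.1² = 445. It allows no starters after T0, and it treats the recently diagnosed stratum as free of bias. With high-risk stopping at 0.35 it falls to 1.4 days.

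Starts before T0 are also possible in the recently diagnosed stratum, and classification at T1 affects both strata, so part of any bias may cancel. This stands, but prior use there is capped at about 3 months and has no cap in the other stratum.

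The analyses are additional and exploratory, time since diagnosis is not among the predefined subgroups, and the primary cohort keeps its restriction. This limits the weight of the point. The protocol does consider misclassification from starts shortly after baseline, but not starts before it.

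Finally, the HF registry section times data collection from diagnosis, which might suggest that no one can be a user before T0. On that reading the stratum diagnosed more than 3 months before baseline would be empty, so the planned comparison itself presupposes otherwise.

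**Conclusion.** The point holds as a risk. Followed as written, these additional analyses place continuing users among the exposed and allow former users into the comparator. Their longer-diagnosed stratum does not match the effect the protocol defines. Whether bias results, how large it is and which way it runs cannot be determined from the documents. On the assumed values above it runs from nil to more than the 3.2 to 3.8 days the study is sized to detect, and it is nil if continuing users do not differ in unadjusted prognosis and former users do not distort the comparator. The main analysis in newly diagnosed patients is not called into question here. This is a cheap improvement to exploratory analyses.

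**What to change.** 1. Restrict the time-since-diagnosis comparison to patients not on telemedicine before T0, with the same rule in both strata. Use the telemedicine start date, or T0 status where no date is held.
2. Reconcile Table 1, which lists telemedicine at T0, with the Exposure measurement section, which names only 6 and 12 months, so that it is clear whether T0 status exists.
3. Report patients already on telemedicine at T0 separately.
4. Add time since diagnosis as a covariate in the pooled entire-cohort models; it is not in the listed adjustment set.
5. Leave the primary cohort and its analysis unchanged.
6. Where neither start date nor T0 status is available, state that the comparison cannot separate timing from selection of continuing users, and limit its interpretation accordingly.

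The cost is a few lines of text and use of items already planned for collection, provided they prove available; the protocol itself warns that most telemedicine data are at hospital level. There are three downsides. The longer-diagnosed stratum will have fewer exposed patients. The recently diagnosed stratum in this comparison may differ slightly from the primary cohort. Former users who stopped before T0 remain unidentified where only T0 status is held.
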